## Abstract

**Background:**

Skin abscesses are a frequent encountered health care problem and lead to a significant source of morbidity. They consequently have an essential impact on the quality of life and work. To date, the type of aftercare for surgically drained abscesses remains under debate. This leads to undesirable practice variations. Many clinical standard protocols include sterile wound dressings twice a day by a home-care service to reduce the chance of a recurrent wound infection. It is unknown, however, whether reinfection rates are comparable to adequate wound irrigation with a nonsterile solution performed by the patient. Our hypothesis is that simple wound irrigation with nonsterile water for postoperative wound care after an abscess is surgically drained is feasible. We assume that in terms of reinfection and reintervention rates unsterile wound irrigation is equal to sterile wound irrigation.

**Objective:**

The primary aim of this study is therefore to investigate if there is a need for sterile wound irrigation after surgically drained spontaneous skin abscesses.

**Methods:**

In a prospective, randomized controlled, single-blinded, single-center trial based on a noninferiority design, we will enroll 128 patients randomized to either the control or the intervention group. The control group will be treated according to our current, standard protocol in which all patients receive a sterile wound irrigation performed by a home-care service twice a day. Patients randomized to the intervention group will be treated with a nonsterile wound irrigation (shower) twice a day. All patients will have a routine clinical control visit after 1, 3, 6, and 12 weeks in the outpatient clinic. Primary outcome is the reinfection and reoperation rate due to insufficient wound healing diagnosed either at the outpatient control visit or during general practitioner visits. Secondary outcome measures include a Short Form Health Survey, Visual Analog Scale, Patient and Observer Scar Assessment Scale, Vancouver Scar Scale, and the EurolQol 5-Dimension Questionnaire. Those questionnaires will be completed at the outpatient control visits.

**Results:**

The trial was started in June 2016 and enrolled 50 patients by article publication. Regarding the adherence to our protocol, we found 10% of loss to follow-up until now. Only 2 patients needed reoperation and only 1 patient needed a change of treatment (antiseptic therapy). Most patients are happy with their randomized treatment but as expected some patients in the sterile group complained about timing problems with their working hours and home-care service appointments. Most patients in the nonsterile group are satisfied being able to take care of their wounds independently although some patients still depend on the home-care service for the wound dressing. We are hoping to have enrolled enough patients by summer 2017. The follow-up will take until autumn 2017, and study results are expected to be published by the end of 2017. This trial is solely supported by the cantonal hospital of Lucerne.

**Conclusions:**

Nonsterile wound irrigation is more likely to be carried out independently by the patient than sterile wound irrigation. Therefore, if nonsterile wound care shows comparable results in terms of reinfection and reintervention rates, patient independence in the aftercare of surgically drained abscesses will increase, patients can return to work earlier, and health care costs can be reduced. In a preliminary, conservative estimation of health care costs, an annual savings of 300,000 CHF will be achieved in our hospital.

**Trial Registration:**

German Clinical Trials Register DRKS00010418; https://drks-neu.uniklinik-freiburg.de/ drks_web/navigate.do?navigationId=trial.HTML&TRIAL_ID=DRKS00010418 (Archived by WebCite at http://www.webcitation.org/6q0AXp5EX)

## Introduction

Skin abscesses are frequent health care problems that often affect young and vital patients. Abscesses can be a significant source of morbidity and can mean an essential limitation of quality of life as well as an incapacity to work [1]. Therefore, timely and sufficient surgical drainage and aftercare is an essential part of care, not only to prevent potential life-threatening complications due to inappropriate therapy (eg, necrotizing fasciitis, toxic shock syndrome, Ludwig’s angina) but also to enable a normal social life and a return to work as soon as possible.

The current literature shows great national and international variability of the surgical method, with incision, excision, or spindle-shaped opening and without essential evidence for the superiority of one of the methods [2,3]. Furthermore some surgeons prefer a primary wound closure with or without antibiotic therapy [4-7].

Regarding the aftercare for open wound treatment, the diversity continues and literature can be found on wound irrigation with sterile fluids, unsterile fluids [8], and antiseptic fluids [9]; antibiotic therapy [5,6]; and use of different wound dressings such as silver-containing hydrofiber [10], hyaluronate hydrogel [11], and essential oils [12]. These different treatment options are combined in various ways, and so far the results regarding reinfection rates and failure of therapy seem to be comparable.

For superficial perianal abscesses, a German consensus grade S3 (evidence- and consensus-based) guideline is available [13] suggesting surgical drainage without specifying the type of drainage (excision, incision, or spindle-shaped opening) due to limited data. For the aftercare, prospective randomized trials are lacking but the consensus recommends periodic wound irrigation with antiseptic fluid or subsequent antibiotic therapy only being necessary in individual cases [14]. Patients are often instructed to change the dressing twice a day and irrigate the wound with a sterile solution. For sterile treatment, the assistance of a home-care service is often needed, which can impair the social life due to frequent appointments. Therefore, the question arises if an alternative method could at least support the independence of the patient and lead to sufficient wound treatment without regular appointments and sterile wound irrigations.

Considering a trend toward cost-effective medicine and a reasonable use of medical infrastructure, it is questionable whether every wound needs to be irrigated with a sterile solution twice a day by a special home-care service. We consider the nonsterile wound irrigation (carried out in the shower) as a potential treatment option that offers independence for the patient. It is expected that patients can carry it out independently or with the help of a family member. Additionally, this could lead to an earlier return to work [8].

We hypothesize that simple wound irrigation with nonsterile water for postoperative wound care is feasible after surgical draining of abscesses. Moreover, we postulate that wound irrigation in the shower (simple wound irrigation) is equal to sterile wound irrigation accomplished by special home-care service teams in terms of reinfection and reintervention rates. Additionally, we claim that patients who irrigate the wound using nonsterile water (shower irrigation) will be more independent and that the overall costs are less compared to sterile water irrigation due to less frequent consultations of the home-care services.

To our knowledge, this is the first prospective randomized trial evaluating the value of postoperative wound irrigation using nonsterile solution in surgically drained abscesses.

## Methods

### Study Design

Based on a noninferiority design, we designed a prospective, randomized, controlled, single-blinded, single-center trial. We present the study protocol in accordance with the Standard Protocol Items: Recommendations for Interventional Trials guidelines [15].

### Study Population

The study includes patients treated for spontaneous soft tissue abscesses in the largest nonuniversity hospital in Switzerland.

Patients with a primary superficial abscess presenting at the emergency department will be eligible for the inclusion if they fulfill all of the followed criteria:

Soft tissue abscess with an indication for surgical drainage18 years or olderSufficient understanding of spoken and written GermanSigned informed consentHospitalization of at least one night to ensure sufficient teaching from the nurse concerning wound management (according to the study protocol)

We will exclude patients if they meet at least one of the following exclusion criteria:

Patients presenting with residual abscesses, abscesses located on the head, or abscesses with a confirmed fistulaPatients suffering from immunodeficiency (eg, HIV infection, leukemia)Patients taking autoimmune therapyPatients not willing or able to sign the informed consentPatients with psychiatric conditionsPatients not able to return for appointments at 1, 3, 6, and 12 weeks

### Preliminary

Essential prestudy preparations are needed to ensure proper inclusion of patients and correct documentation of the preoperative situation.

#### Defining Period

Standard preoperative documentation of the abscess and its surrounding is necessary to ensure sufficient surgical drainage and to enable comparability between both groups. An abscess was defined as an enclosed collection of liquefied tissue, known as pus, affecting the subcutaneous tissue and representing the immune defense reaction of the body against foreign material or bacteria. As seen in Figure 1, the abscess consists of (1) the area of fluctuation caused by the collection of liquefied tissue, (2) the area of cellulitis caused by hyperemia due to an immune reaction of the body, and (3) the area of induration caused by the hardening of the soft tissue due to the inflammation.

We also defined provisions that needed to be followed to ensure proper surgical drainage during our trial: (1) the incision of the skin has to be at least as long as the fluctuation, (2) the incision of the skin has to be spindle-shaped to ensure a wide opening of the abscess cavity, and (3) the spindle-shaped incision has to include at least two-thirds of the width of the fluctuation.

#### Implementation Period

An educational period teaching basic facts about abscesses will be initiated before the inclusion period starts. All surgeons treating the above mentioned conditions will participate in a special lecture about the pathophysiology, diagnosis, and management of abscesses. We defined the necessity for documentation of the following parameters (see Figure 1): the diameter of the fluctuation and hyperemia and photo documentation with a scale. Finally, everyone involved received handouts containing all relevant information.

### Randomization

Prior to the operation, patients are being randomized either to the control or the intervention group using sealed envelopes. The randomization will be carried out after the signed informed consent is obtained.

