#### Intervention Group (Group II)

Patients belonging to the intervention group are treated according to a modified aftercare protocol. We recommend shower irrigation for the nonsterile treatment twice a day. The patient is recommended to use a shower with room temperature water and irrigate the entire wound cavity with gentle pressure for 1 to 2 minutes using water only. The use of shower gel, soap, or shampoo is forbidden. After wound irrigation, the dressing of the wound with a moist and unfolded gauze followed by a dry nonsterile gauze and tape is carried out similar to the control group.

The first postoperative wound dressing is changed by the nurse and surgeon on the ward. The patient and/or family members are trained to adequately manage the wound and change the dressings. In case the patient is unable to change the dressing alone, the same home-care service is requested to support the patient. The home-care service is informed with a standard form.

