### Outpatient Control Visits

All patients receive a standard postoperative outpatient control visit after 1, 3, 6, and 12 weeks. All questionnaires except the VSS and the POSAS will be answered during each visit as shown in Table 1. The VSS and POSAS will be used at the 12-week control visit as definite wound healing is needed to answer these questionnaires. As this is a single-blinded trial, it is essential to ensure blinding of the investigator at the outpatient control visit. All outpatient follow-ups will be carried out by two blinded surgeons investigating the wound and filling out the questionnaire.

**Table 1 table1:** Timeline of outcome measurements.

		Study period					
		Enrollment	Allocation	Outpatient control			
		ED^a^	Operation	Week 1	Week 3	Week 6	Week 12
Enrollment							
	Inclusion criteria	X					
	Informed consent	X					
	Randomization	X					
	Patient baseline characteristics	X					X
Interventions							
	Control group	X	X	X	X	X^b^	X
	Intervention group	X	X	X	X	X^b^	X
Assessments							
	SF-36^c^	X		X	X	X^b^	X
	VAS^d^	X		X	X	X^b^	X
	EQ-5D^e^	X		X	X	X^b^	X
	Medical questionnaire	X		X	X	X^b^	X
	VSS						X
	POSAS						X

^a^Emergency department.

^b^Optional outpatient control, only necessary if wound still open at 3 weeks control.

^c^SF-36: Short Form Health Survey.

^d^VAS: Visual Analog Scale.

^e^EQ-5D: EuroQol 5-Dimension Questionnaire.

^f^VSS: Vancouver Scar Scale.

^g^POSAS: Patient and Observer Scar Assessment Scale.

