### Statistical Analysis

Statistical analysis will be performed using SPSS version 21 (IBM Corp). The mean and standard deviation will be calculated and reported for basic patient-related data. Primary analysis will be carried out comparing frequency of reintervention between the intervention and control groups. Moreover, we will try to identify risk factors as basic patient-related data or surgery-associated factors (time of surgery, operation time, experience of the surgeon) using regression models.

Secondary clinical outcome measures will be presented in means with the corresponding standard deviation. The intervention group and the control group will be compared using mean value analysis models (*t* test; multifactorial mean value analysis). We will assume that data missing will be random; therefore, missing data will not be imputed, as we will use the mixed model approach for the longitudinal analyses.

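### Randomising before surgery, when the arms differ only in aftercare, leaves the operation and the overnight-stay criterion open to knowledge of the arm

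*Protocol article*

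**What the plan says.** The Randomization section states: "Prior to the operation, patients are being randomized either to the control or the intervention group using sealed envelopes". It adds: "The randomization will be carried out after the signed informed consent is obtained". Table 1 ticks randomisation, consent and the inclusion criteria in the emergency department column.

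The sections on the control and intervention groups describe treatments that differ only after the operation: sterile irrigation supported by home care, or shower irrigation with nonsterile dressing. The arm-specific care begins in hospital: "The first postoperative wound dressing is changed by the nurse and surgeon on the ward". Training of the patient or family follows.

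On blinding, Outpatient Control Visits says: "As this is a single-blinded trial, it is essential to ensure blinding of the investigator at the outpatient control visit". It continues: "All outpatient follow-ups will be carried out by two blinded surgeons investigating the wound and filling out the questionnaire". No other role is described as blinded.

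Study Population makes inclusion conditional on hospitalisation "of at least one night to ensure sufficient teaching from the nurse concerning wound management".

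Defining Period sets three rules for the incision: a minimum length, a spindle shape, and that "the spindle-shaped incision has to include at least two-thirds of the width of the fluctuation". Implementation Period adds a lecture for all treating surgeons, handouts, recorded diameters and photographs with a scale.

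**The concern.** Allocation is fixed at a point where neither arm needs it. Between that point and the start of arm-specific care lie two events that could be affected by knowing the arm.

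The first is the operation. The endpoint is reinfection or reoperation within 12 weeks of drainage, and the article itself treats adequate and comparable drainage as something to secure in both groups. If a surgeon who knew that a wound would be showered drained it differently, the effect of aftercare would be mixed with an effect of surgery. In a noninferiority trial, a change that lowered the event rate in the shower arm would favour the conclusion the trial hopes to reach.

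The second is completion of the overnight stay. It exists for wound-care teaching, and the teaching of patients and families is described only for the intervention arm. Staff who know the arm could discharge the two arms differently. Any exclusions that followed would come after randomisation and might be unequal between arms.

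**Working it through.** The timing question is settled by reading the sections together. The arithmetic afterwards only shows how sensitive the trial would be under assumed sizes.

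**Sequence**

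1. Consent, then randomisation: before the operation (Randomization; emergency department column of Table 1). The Table 1 header places the word allocation over the operation column. On that reading, too, allocation is no later than surgery.
2. Operation: governed by the Defining Period rules. Length and width are minimums; the shape is fixed. A surgeon may exceed the minimums.
3. First dressing change and teaching: on the ward. This is the first step at which the arms differ.
4. Overnight stay completed: after step 1, and therefore after allocation.
5. Blinded assessment: outpatient visits from week 1.

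The stated blinding covers step 5 only. Steps 2 and 4 fall after allocation with no stated safeguard.

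**Reference point for the illustrations**

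Inputs from Sample Size Calculation: 58 evaluable per arm, power 0.80, alpha 0.05, a 15% rate, and 10% loss, so 58 × 1.10 = 63.8, rounded to 64 per arm and 128 in total. The article labels no margin and does not say whether alpha is one- or two-sided. I therefore assume 15% in both arms and derive the margin that 58 per arm would imply:

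Δ = (z₁₋α + z₀.₈₀) × √(2 × 0.15 × 0.85 / 58)

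- One-sided 0.05: (1.645 + 0.842) × 0.0663 ≈ 0.165.
- One-sided 0.025: (1.960 + 0.842) × 0.0663 ≈ 0.186.

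**Illustration 1: arm-dependent surgery (assumed effect b)**

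Set the true intervention rate, without any surgical effect, at 0.15 + Δ, so that noninferiority is false. Let arm-aware surgery lower it by b, giving p = 0.15 + Δ − b and SE = √[(0.15 × 0.85 + p(1 − p)) / 58]. The chance of a false noninferiority finding is Φ(b/SE − z₁₋α).

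| Assumed b (percentage points) | One-sided 0.05 | One-sided 0.025 |
|---|---|---|
| 0 | 5.0% | 2.5% |
| 1 | 6.5% | 3.4% |
| 2 | 8.4% | 4.5% |
| 3 | 10.6% | 5.8% |
| 5 | 16.5% | 9.7% |

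Nothing in the article says that b differs from zero. The table shows only that a small difference would matter.

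**Illustration 2: post-randomisation exclusions (assumed fraction)**

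After 10% loss, 64 × 0.90 = 57.6 per arm remain. Power is Φ(Δ / √(2 × 0.15 × 0.85 / n) − z₁₋α).

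| Assumed further exclusion | Evaluable per arm | Power, one-sided 0.05 | Power, one-sided 0.025 |
|---|---|---|---|
| 0% | 57.6 | 80% | 80% |
| 5% | 54.7 | 78% | 78% |
| 10% | 51.8 | 76% | 75% |

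The loss of power is modest. If exclusions occurred, the larger problem would be any imbalance between arms.

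**The case against.** The strongest reply is that this argues from what a condensed article leaves out. It does not say who opens the envelope, exactly when, or whether the operating surgeon is told; such operational detail may stand in the full protocol. That is right as far as it goes. A reader might infer that the surgeon does know the arm, and the text does not support that. What stands is that the article itself fixes the order of randomisation and surgery, and that order creates the exposure.

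Surgery is also partly standardised. The minimum incision rules guard against inadequate drainage, and the training, measurements and photographs add control. These are real safeguards, but they set floors rather than an exact extent, and the measurements and photographs that the article specifies concern the abscess before surgery.

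Three stronger readings fail:

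- A reader might count fistulas found at operation as a second source of exclusion after allocation. The criterion concerns patients presenting with a confirmed fistula, and nothing says that one found later leads to exclusion.
- A reader might suppose that ineligible patients who are kept would go untreated. Both regimens continue at home, so early discharge shortens ward teaching but does not withhold the allocated irrigation.
- A reader might take Statistical Analysis as showing that the extent of drainage drives reinfection. It plans an exploratory search among "surgery-associated factors (time of surgery, operation time, experience of the surgeon) using regression models", and incision extent is not on the list.

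On the overnight stay, Table 1 ticks the inclusion criteria in the emergency department, so an expected stay may be what is judged there. No rule drops a patient discharged early, and the Results section, reporting on 50 enrolled patients, mentions no such exclusion. The criterion as worded is nevertheless the stay itself.

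**Conclusion.** The point holds as an avoidable risk of bias built into the stated sequence. Randomisation precedes surgery without a need that the article states, no safeguard is given for the operating surgeon, and one inclusion criterion is literally completed after allocation. It is not evidence that bias has occurred or that any patient has been wrongly excluded.

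The size cannot be calculated from the document. The illustrative figures rest on assumed surgical effects and exclusion fractions, and on a margin derived from 58 per arm because none is labelled. They should not be read as estimates. The case for acting is that the remedy is cheap and that later adjustment is a poor substitute: the planned regression does not name incision extent, and no model restores patients excluded after allocation.

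**What to change.** For patients still to be enrolled, keep consent and eligibility screening in the emergency department. Open the sealed envelope after the operation, on the ward, before the first dressing change and teaching, once the overnight stay is confirmed. Amend the Randomization section and the randomisation row of Table 1 to match. Keep all patients already randomised and analyse them in their allocated arm.

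Treatments, endpoint and sample size are unchanged: 58 evaluable per arm and 128 randomised.

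The cost is an amendment and two practical drawbacks. Ward staff must hold and open the envelopes. About 50 of 128 patients (50/128 = 39%) will have been randomised at the earlier point and the remaining 78 at the later one, which should be stated when the trial is reported.

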**Figure 1 figure1:**
[figure not shown]
Definition of the area of hyperemia (red) and fluctuation (central frame) with a ruler to indicate the size of the areas.

#### Control Group (Group I)

Patients belonging to the control group will be treated according to our current protocol, including sterile wound treatment supported by a home-care service. We recommend a standard of sterile wound irrigation twice a day using either Ringer’s lactate or normal saline solution. The wound, including the whole cavity, should be irrigated 3 to 5 times with a 20 mL syringe, treating the whole wound surface with gentle pressure. Thereafter, a moist and unfolded gauze is inserted in the cavity. The unfolded gauze develops a bigger osmotic pressure and therefore ameliorates the suction effect on the cavity. Subsequently the wound should be dressed in a sterile way using gauze and tape to fix the dressing. The home-care service is informed with a standard form.

